
#### Sample size

A power calculation to determine a sample size is not appropriate for a feasibility trial, as the purpose of the trial is not to establish efficacy. However, the data from this trial could be used to inform a sample size calculation for a later efficacy pilot trial. The target recruitment for this feasibility trial will be *N* = 60 (30 in each arm).This was determined with reference to existing studies in the field and is consistent with good practice recommendations for feasibility/pilot studies [13, 14].

### Description of therapies

Therapy sessions in both conditions will be delivered on an individual basis in a private room on an inpatient ward. The trial therapist in both conditions will be PJ, who is a Clinical Psychologist registered with the UK Health and Care Professions Council (HCPC) and has expertise in cognitive behavioural therapy for psychosis (CBTp) and mindfulness interventions as well as experience of working in acute settings. Although not matched on a case by case basis, therapy sessions in both conditions will range from one to five sessions, depending on length of admission, with the frequency of sessions adjusted as needed between a minimum of weekly and maximum of daily. All sessions will follow a stand-alone, self-contained format in order to accommodate unpredictable lengths of stay and unexpected discharges. Participants in the trial will continue to receive treatment as usual (TAU) both during their inpatient admission and post-discharge. In practice, this may include medication, attendance at activity and/or therapy groups, individual therapy sessions and family therapy sessions.

#### Mindfulness-Based Crisis Interventions (MBCI)—experimental intervention

MBCI was developed in line with the model of mindfulness for psychosis proposed by Chadwick [10]. People who experience positive psychotic symptoms (e.g. voices, paranoid thoughts) often respond by trying to avoid experiences (experiential avoidance) or at the other end of the spectrum, by getting lost in engaging with them (rumination, confrontation). Mindfulness offers an alternative way of responding, with acceptance and non-judgemental awareness in each moment, allowing psychotic symptoms to move in and out of awareness without the person getting caught up in struggling against them. The treatment protocol for the current trial was adapted for use within an acute crisis setting, partly based on PJ’s clinical experience of working within inpatient settings and in consultation with ACT experts in the USA, including the lead author of one of the key inpatient trials [6].

There are three key components to be included in each session:i.Developing mindfulness skills (guided practice)ii.Making sense of crisis using mindfulness modeliii.Identifying values and setting goals

A typical session will start with a 5-min mindfulness practice, including frequent guidance that includes reference to psychotic experience and uses everyday, concrete language. The therapist will then move on to developing a collaborative understanding with the participant of what has brought them to a hospital on this occasion, focussing on how they usually try to cope with difficult voices, thoughts, feelings and experiences and how well these strategies are working for them. Given the time constraints, therapists will share a formulation and example strategies (following Chadwick [10]), asking the participant to connect with and provide examples of his or her own habitual reactions. In line with the formulation, the therapist will highlight the participant’s attempts to either block out, suppress or otherwise escape from unwanted internal experiences or reactions that mean getting caught up in struggling with internal experiences (rumination, fighting). Mindfulness is located as a middle way between these two reactive styles. Finally, the therapist will work with the participant to identify their values (e.g. family, work, health, society) and discuss specific behavioural goals consistent with these values. Participants are then helped to set a small, achievable goal for homework at the end of each session which can be reviewed at the beginning of next session, where possible. In preparation for discharge, longer-term goals can also be identified (e.g. starting a college course) and will be shared with the community care team at the end of therapy, to act as a bridge to carrying on the recovery process in the community.

#### Social activity therapy (SAT)—control intervention

This control condition is taken from the PICASSO trial of CBTp for people with psychosis and a history of violence and was conducted partly on inpatient wards [15]. SAT involves collaboratively working with the participant to identify activities they enjoy and which they can engage in during sessions and between sessions as they wish (e.g. board games, puzzles). The aim is to provide a supportive environment with a therapist using non-specific aspects of therapy (e.g. agenda setting, collaboration, feedback, empathy). The therapist aims to keep the sessions activity focussed and to be supportive, collaborative and empathic without employing any therapy techniques specific to any model of therapy, including CBTp or mindfulness-based therapies.

#### Treatment fidelity

The trial therapist will receive regular supervision from an independent clinical supervisor with expertise in acute care and mindfulness-based approaches. Therapy sessions will be audio-taped with participant consent (the proportion of participants who consent to audio-recording will also be recorded and reported as part of the trial outcomes). A sample of therapy sessions will be assessed by a blinded and independent rater for therapy fidelity. An adherence and competency scale for the trial has been developed for this purpose, based on existing scales from other therapy trials [15–17] and relevant theoretical papers and therapy manuals [7, 10, 18].

### Outcome measures

#### Primary objective—feasibility/acceptability data

Number of eligible participants identified over study periodTotal numbers recruited into trial and recruitment rate (benchmark of 80 % of target)Proportion of participants who drop out during the intervention stageRange and average number of sessions completed (including number of sessions attended as a proportion of those offered)Reasons for participants dropping out during the intervention stageNumber lost to follow-up and reasons (benchmark of less than 20 % to be set in line with previous studies)Any unexpected adverse effects of participating in the trial

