## Methods/design

### Study design and timeline

This study is a single-centre, parallel-groups, feasibility randomised controlled trial. Trial procedures and the assessment schedule are shown in the study plan (Fig. 1). In brief, service use data (re-hospitalisation rate, use of crisis team, relapse rate) will be collected using case note review at 3- and 6-month follow-up. Self-report clinical measures will be taken at baseline, post-therapy and at 3-month (mid-point) and 6-month follow-up after discharge (end-point). The 3-month mid-point follow-up was included in order to minimise missing data arising from loss to follow-up and to provide more detailed information on symptom change in the short-term after discharge. The service use data will provide information on the appropriateness and sufficiency of re-admission as the primary outcome measure for future efficacy trials or whether an additional primary outcome would be indicated (e.g. relapse rate from case note review). The trial will also provide important data on the acceptability and utility of the self-report clinical measures, for example, whether participants are willing and able to complete the measures and whether they show sensitivity to change over time.

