#### Secondary objective—pilot data

Pilot outcome measures (service use and clinical measures) will be collected, as detailed in Table 1. A cost-effectiveness analysis of the intervention is outside the scope of this feasibility study; however, the service-use data collected would be relevant to the future assessment of economic costs. This is in addition to data on therapy costs which will be collected, such as the average number of sessions received per participant.

**Table 1 Tab1:** Summary of outcome measures

Pilot data—inpatient/crisis service use			
Outcome		Method	Time period
Primary outcome:			
1) Re-hospitalisation (≥1 OBD)		Clinical notes	Discharge—3- and 6-month follow-up
Secondary outcomes:			
2) Time to re-admission (days)		Clinical notes	Discharge—3- and 6-month follow-up
3) Total number of OBDs		Clinical notes	Discharge—3- and 6-month follow-up
4) Episodes of care with crisis/home treatment team		Clinical notes	Discharge—3- and 6-month follow-up
5) Contact with CMHT (number of meetings/contact with CMHT including care co-ordinator)		Clinical notes	Discharge—3- and 6-month follow-up
6) Reference to therapy goal which was shared with team		Clinical notes	Discharge—3- and 6-month follow-up
7) Relapse rate		Clinical notes	Discharge—3- and 6-month follow-up
Pilot data—clinical measures			
Construct assessed	Questionnaire	Method	Time points
Credibility of therapy	1) Therapy credibility	Self-report	Baseline only (immediately post-randomisation)
In the moment rating of stress and interference from symptoms and hope for the future	2) Stress bubbles	Self-report	At the beginning and end of every therapy session
Frequency, distress and believability of most distressing symptom	3) Self-ratings of psychotic symptoms (based on Bach and Hayes, 2002; Gaudiano and Herbert, 2006)	Self-report	Baseline, end of therapy, 3-month mid-point and 6-month follow-up
Mood—depression, anxiety and stress	4) DASS-21 (Depression, Anxiety and Stress Scale; Lovibond and Lovibond, 1995)	Self-report	Baseline, end of therapy, 3-month mid-point and 6-month follow-up
Self-defined recovery	5) QPR (Questionnaire about the Process of Recovery; Neil et al 2009)	Self-report	Baseline, end of therapy, 3-month mid-point and 6-month follow-up
Voices (incl. frequency, distress, interference and compliance)	6) HPSVQ (Hamilton Program for Schizophrenia Voices Questionnaire; Van Lieshout and Goldberg, 2007)	Self-report	Baseline, end of therapy, 3-month mid-point and 6-month follow-up

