### Analysis plan

Descriptive statistics will be reported for the key outcomes on the feasibility data (including mean averages, standard deviations and ranges where appropriate). Flow through the trial will also be presented in a standard CONSORT diagram, showing number approached to participate, number randomised, drop-outs before the end of treatment and numbers retained in the trial at 3- and 6-month follow-up. Pilot data on the primary outcome of re-hospitalisation at 6-month follow-up will be analysed using survival analysis. The proportion *n* (%) of patients readmitted at 3 and 6 months will be reported, with the difference in time to re-admission between intervention and control groups being formally compared using Kaplan-Meier/Log rank survival analysis. Odds ratios with 95 % confidence intervals will be calculated and used to provide an indicator of measurement precision. This will help provide information on the appropriateness of re-admission as the primary outcome measure for future trials. In order to provide data for future sample size calculations, pilot data on clinical measures will be analysed using the general linear model, co-varying for baseline score and treatment condition. All analyses will be done on an intention-to-treat principle, in consultation with the KCTU. As this is a feasibility study, it is not powered to detect treatment efficacy and accordingly all hypothesis testing should be treated as preliminary and interpreted with caution.

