### Conclusion

In summary, the results of this feasibility trial will indicate whether a subsequent efficacy pilot RCT is warranted and, if so, will provide vital information for the planning of such a trial. If future research finds that MBCI is an effective and safe intervention, then patients will benefit from access to better treatment within inpatient care which could help them stay out of hospital for longer after discharge. This would also help NHS mental health trusts to deliver more cost-effective inpatient care as savings would be made over the longer-term due to reduced service use by patients.

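### The only harms outcome counts an event only if it is unexpected and an effect of participating, so serious events on the ward judged expected or unrelated could go uncounted

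*Protocol article*

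**What the plan says.** Under Outcome measures, the list for the primary (feasibility and acceptability) objective ends with "Any unexpected adverse effects of participating in the trial". No other outcome in the article is labelled as harm, and none names self-harm, suicide attempt, violence, death or serious adverse events as a class.

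Separately, Study design and timeline states that "service use data (re-hospitalisation rate, use of crisis team, relapse rate) will be collected using case note review at 3- and 6-month follow-up". Table 1 lists these items, among them "1) Re-hospitalisation (≥1 OBD", "4) Episodes of care with crisis/home treatment team" and "7) Relapse rate". All come from clinical notes over the period from discharge to 3 and 6 months, with no condition of expectedness or cause.

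Under Recruitment, randomisation and blinding, the person mainly responsible for gathering the trial data is not blinded, independent staff may collect some follow-up data, and the study is to follow Good Clinical Practice. Description of therapies makes that same person the therapist in both arms and places the sessions on the ward.

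**The concern.** The harms item has two entry conditions, and both call for a judgement on each case. The article itself describes people admitted in crisis, some of them detained, and excludes those whose risk of aggression or violence rules out individual therapy. In such a population a serious event can readily be classed as part of the illness (expected) or as nothing to do with the trial (unrelated). Either label removes it from the count, however such events divide between the arms.

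A randomised comparison with an active control does not need that judgement: all serious events can be counted in each arm and the counts compared. With the conditions as entry filters, that advantage is lost for the events that matter most. The Conclusion says the results will inform whether a further trial should go ahead, so a low count produced by the filters could be read as reassurance that it does not give.

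**Working it through.** The article states no harm rate and no power calculation, so there is no figure to reproduce. The main check is to compare which outcomes would pick up a serious event, and when.

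| Outcome | Period covered | Expectedness or cause filter | Names self-harm, suicide attempt, violence or death |
|---|---|---|---|
| Harms item in the feasibility list | Not stated | Both | No |
| Re-admission, bed days, crisis-team episodes, relapse (Table 1) | Discharge to 3 and 6 months | None | No |
| Self-report symptom and mood scales (Table 1) | Baseline, end of therapy, 3 and 6 months | None | No |
| Stress, interference and hope ratings (Table 1) | Start and end of each session | None | No |

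1. After discharge, a serious event leading to re-admission, crisis-team care or relapse is captured whatever its cause. For re-admission the Analysis plan has the "difference in time to re-admission between intervention and control groups being formally compared using Kaplan-Meier/Log rank survival analysis".
2. Between randomisation and discharge, when therapy is delivered, none of the unfiltered service-use items applies. A serious event in this period reaches a harms count only through the filtered item.
3. The self-report scales do follow symptoms on the ward, but they are scores and do not record events.

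**What a filtered zero can hide (illustration).** The arm size of 30 is from Sample size. The other inputs are assumptions: p is the proportion of an arm with at least one serious event, and f is the share of those participants whose event passes both filters. Then

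P(zero counted) = (1 − p × f)^30

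| p × f | P(zero counted) | Share passing if p = 20% | Share passing if p = 10% |
|---|---|---|---|
| 20% | 1 − 0.9988 = 0.1% | all | – |
| 10% | 1 − 0.9576 = 4.2% | half | all |
| 5% | 1 − 0.7854 = 21.5% | a quarter | half |
| 2% | 1 − 0.4545 = 54.5% | a tenth | a fifth |
| 0% | 100% | none | none |

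At p = 20%, 30 × 0.20 = 6 participants per arm would be expected to have an event, yet a reported zero becomes more likely than not once only a tenth pass.

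**Precision, as context.** Even an unfiltered 0 of 30 leaves a two-sided 95% exact upper limit of 1 − 0.025^(1/30) = 11.6% (one-sided: 1 − 0.05^(1/30) = 9.5%). This limit reflects the arm size and would remain after the rewording. A filtered zero sets no limit at all on the rate of expected or unrelated serious events.

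**The case against.** The strongest reply is that this is one line in a condensed article. It names a reported outcome and does not set out a recording procedure. Definitions and logging of adverse events usually sit in the full protocol, and the article commits to Good Clinical Practice, a data management plan and a steering committee. That stands against any inference that serious events would go unrecorded. It does not remove the point, which concerns how a stated outcome is defined.

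The word unexpected is also open. The article has no list of expected events and does not say that self-harm or violence belongs on one; the phrase could mean any unanticipated harm from taking part. That is fair, and it is why events *may* be left out. But an outcome that can be read either way is itself a reason to reword it.

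Several stronger readings are tempting and are not supported:
- *Relapse-related crises would go uncounted.* Relapse, re-admission and crisis-team episodes are collected for all participants after discharge without filters.
- *Worsening symptoms would be invisible.* Self-report scales track symptoms and mood at four time points, and ratings are taken at every session. Reasons for drop-out and the feedback interviews give further routes.
- *The therapist decides what is attributed.* The article says who mainly gathers the data and does not say who judges expectedness or relatedness.
- *An absence of harm would be falsely reported.* No safety claim is planned. The Conclusion leaves that to later work ("If future research finds that MBCI is an effective and safe intervention"), and the article sets no safety rule for progression.

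**Conclusion.** The concern holds in a limited form. The harms outcome as worded admits only events that are unexpected and effects of participation. Serious events judged otherwise may therefore be missing from an account of harms by arm. The gap is clearest between randomisation and discharge, where the unfiltered service-use items do not apply. After discharge it is narrower: serious events that lead to no re-admission, crisis-team care or relapse.

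The size cannot be fixed from the article, because neither the rate of serious events nor the share that would pass the filters is given. Under the assumed rates of 10% and 20%, the chance of a counted zero in an arm of 30 runs from 4.2% and 0.1% with no filtering to 100% if nothing passes. The conclusion assumes that the item is applied as written and that the full protocol does not define it more widely. That the unblinded therapist for both arms gathers most of the data makes a count resting on judgement weaker, even though the assessor is not named.

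**What to change.** Reword the last item of the feasibility list along these lines: *All serious adverse events from randomisation to 6 months after discharge, extracted from case notes for every participant and tabulated by arm, with expectedness and relatedness recorded as attributes and not used as entry filters.* Name the events of most interest (death, suicide attempt or self-harm, violence) so that extraction is uniform.

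The cost is a few extra fields in the case-note review already planned at 3 and 6 months, with the review extended back from discharge to randomisation. The trial status is given as in preparation, so the change can be made before recruitment. It does not improve precision: with 30 per arm, the counts will remain descriptive.

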#### Qualitative data on acceptability

Participant feedback on trial procedures, randomisation and credibility of two therapiesStaff feedback on trial procedures, recruitment strategies and blinding procedures

At the end of the study, participants will be asked if they are willing to give feedback on trial procedures and therapy by way of a follow-up interview or focus group. Participation will be optional. The feedback interviews/focus groups will be conducted by an appropriately trained service user researcher. Staff from the inpatient units where patients were recruited will also be invited to give feedback on the trial via interview or focus group and will be asked to give informed written consent. Interviews and focus groups will be audio-recorded, with written consent from all participants. Qualitative data will be analysed using thematic analysis [19], which is a commonly used approach within applied health research. The data will be initially coded line-by-line to identify emergent themes, which will then be grouped together into larger themes and sub-themes. The data will be coded by at least two people, in order to allow some degree of inter-rater reliability.

#### Secondary objective—pilot data

Pilot outcome measures (service use and clinical measures) will be collected, as detailed in Table 1. A cost-effectiveness analysis of the intervention is outside the scope of this feasibility study; however, the service-use data collected would be relevant to the future assessment of economic costs. This is in addition to data on therapy costs which will be collected, such as the average number of sessions received per participant.

**Table 1 Tab1:** Summary of outcome measures

Pilot data—inpatient/crisis service use			
Outcome		Method	Time period
Primary outcome:			
1) Re-hospitalisation (≥1 OBD)		Clinical notes	Discharge—3- and 6-month follow-up
Secondary outcomes:			
2) Time to re-admission (days)		Clinical notes	Discharge—3- and 6-month follow-up
3) Total number of OBDs		Clinical notes	Discharge—3- and 6-month follow-up
4) Episodes of care with crisis/home treatment team		Clinical notes	Discharge—3- and 6-month follow-up
5) Contact with CMHT (number of meetings/contact with CMHT including care co-ordinator)		Clinical notes	Discharge—3- and 6-month follow-up
6) Reference to therapy goal which was shared with team		Clinical notes	Discharge—3- and 6-month follow-up
7) Relapse rate		Clinical notes	Discharge—3- and 6-month follow-up
Pilot data—clinical measures			
Construct assessed	Questionnaire	Method	Time points
Credibility of therapy	1) Therapy credibility	Self-report	Baseline only (immediately post-randomisation)
In the moment rating of stress and interference from symptoms and hope for the future	2) Stress bubbles	Self-report	At the beginning and end of every therapy session
Frequency, distress and believability of most distressing symptom	3) Self-ratings of psychotic symptoms (based on Bach and Hayes, 2002; Gaudiano and Herbert, 2006)	Self-report	Baseline, end of therapy, 3-month mid-point and 6-month follow-up
Mood—depression, anxiety and stress	4) DASS-21 (Depression, Anxiety and Stress Scale; Lovibond and Lovibond, 1995)	Self-report	Baseline, end of therapy, 3-month mid-point and 6-month follow-up
Self-defined recovery	5) QPR (Questionnaire about the Process of Recovery; Neil et al 2009)	Self-report	Baseline, end of therapy, 3-month mid-point and 6-month follow-up
Voices (incl. frequency, distress, interference and compliance)	6) HPSVQ (Hamilton Program for Schizophrenia Voices Questionnaire; Van Lieshout and Goldberg, 2007)	Self-report	Baseline, end of therapy, 3-month mid-point and 6-month follow-up
Mindfulness	7) SMQ (Southampton Mindfulness Questionnaire; Chadwick et al, 2008)	Self-report	Baseline, end of therapy, 3-month mid-point and 6-month follow-up

*OBD* occupied bed day, *CMHT* community mental health team

